**Fig. 2 Fig2:**
[figure not shown]
Intervention algorithm

### Ethics

The Scientific and Ethics Committees of the HUNSC approved the study protocol. The study is being performed in accordance with Good Clinical Practice Standards, applicable local regulatory requirements, and the recommendations of the Declaration of Helsinki.

### Endpoints

#### Primary endpoint

The primary endpoint of this study is the difference in mean length of hospital stay between the two compared groups. A difference of 2.6 days is considered clinically significant [13].

#### Secondary endpoints

##### Mortality and morbidity

Rate of mortality in in-hospital patients.Rate of mortality in the course of three months post-discharge.Comorbidity will be assessed using the Charlson Index (CI) [14], which comprises 19 categories of the International Classification of Diseases, (10th revision) diagnose codes (ICD-10). It is based on a set of risk factors for the 1-year mortality risk and can be applied to establish the association between the life expectancy of a patient and the resources a health care system must allocate.

##### Complications

Readmission rates, i.e., within 3 months post-discharge.Rate of surgical interventions during hospital stay.Incidence of clinical in-hospital complications according to the Classification of Hospital-Acquired Diagnoses (CHADx) [15]. The CHADx tool is a hierarchical classification of encoded diagnoses based on the International Classification of Diseases-10 (ICD-10), which allows quantification of the burden of in-hospital complications.Surgical complications according to the Clavien-Dindo classification, a standardized and internationally validated scoring system. The system allows for the severity of the complication and its interference in the clinical course of the operated patients. The highest grade complication (grades I-V) experienced by each patient was recorded [16].

##### Treatment

Rate of prescribed nutrition treatments.Period prior to nutrition treatment.Characteristics of the nutrition treatment (duration, type, indications, prolongation following discharge, changes in the treatment, number of visits of the dietitian, and number of referrals).

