### Subjects

Patient inclusion criteria:Patient admitted to the hospitalization ward of Internal Medicine or General and Digestive Surgery of the HUNSC.Formal consent to participate in the study.Age of 18 or more years.

Patient exclusion criteria:Patient treated with nutrition support before finishing the CIPA screening procedure.Patient transferred from other ward.Patient with an expected length of stay of less than 72 h.Unfeasible CIPA screening for whatever reason.Patient with poor short-term prognosis.Bed assignment at hospital admission non-randomized.Patient participating in other research study.Pregnancy.

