### Setting and recruitment

Patients were recruited in the hospitalization area of the HUNSC, in the wards of Internal Medicine and General and Digestive Surgery. These departments were chosen for integrating the patients with the highest clinical variability and comorbidity. Recruitment was conducted in two phases: the first, at the time of hospitalization, in which the patient was confirmed to meet the inclusion or exclusion criteria and asked to sign the informed consent, thereby becoming potentially eligible. The second phase took place at 72 h, when the result of the CIPA nutrition screening was obtained, point at which the patient was verified not to have received nutrition treatment by that time and eventually became part of the sample. Otherwise, the patient was excluded from the study according to criterion 1).

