##### Biochemical determinations

Plasma albumin was determined by colorimetry, using a Roche/Hitachi Cobas C 702 Autoanalyzer (Roche Diagnostics). This parameter was requested automatically within 48 h post-admission. Results are expressed in g/dL.

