##### Anthropometric determinations

BMI: Weight (kg) and height (cm) were obtained with the patient barefoot, dressed in hospital pajamas, using calibrated Seca 220 scales that include a height rod. In the case of patients confined to bed, where weight and height could not be determined, MUAC (cm) was obtained on the patient’s non-dominant arm, at the midpoint between the acromion and olecranon, surrounding the arm with a measuring tape (Seca 201) without pressing the limb. This data was collected by nurses and nursing assistants, when the patient entered the hospital ward, and was then transferred to the electronic medical record (EMR).

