#### Statistical analysis

Descriptive data analysis will present qualitative variables as frequencies and percentages, and continuous variables as means, medians, and standard deviations. Normality shall be verified by the Kolmogorov-Smirnov normality test. In bivariate analysis, depending on the nature of the variables, the parametric hypothesis test Student’s *t*-test or the non-parametric Mann-Whitney test will be used. To assess the effects of the intervention, changes in the primary and secondary outcomes will be analyzed by a between-group ANCOVA variance test. The analysis will control for the type, age, and sex of the patient, as well as the responsible medical unit. Patients admitted to Internal Medicine will be categorized into the four groups (1) cardiovascular, (2) neoplastic, (3) infectious, and (4) other patients, whereas patients in the Digestive and General Surgery services will be divided into the categories (1) neoplastic, (2) infectious, (3) obstructive, (4) inflammatory, and (5) others. The economic evaluation and statistical analyses of individual variables will be conducted in accordance with the intention-to-treat principle.

All tests will be two-sided with a type I error of 5%. Statistical analyses will be performed using the Statistical Package for Social Sciences (SPSS v.23, Chicago, IL, USA).

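### Time to nutrition treatment exists only in treated patients, so the planned ANCOVA on it is not a randomised comparison, and it cannot see treatment started inside the 72 h window

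*Protocol article*

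**What the plan says.** Under Secondary endpoints, Treatment, the article lists "Rate of prescribed nutrition treatments" and, separately, "Period prior to nutrition treatment". The first entry implies that not everyone is treated. The second gives no time origin, no population and no rule for patients who are never treated.

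Under Statistical analysis the general rule is that "changes in the primary and secondary outcomes will be analyzed by a between-group ANCOVA variance test". Student's t-test or Mann-Whitney is allowed for bivariate work, and intention to treat is stated as the principle. No time-to-event method is named.

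Under Subjects, the first exclusion is "Patient treated with nutrition support before finishing the CIPA screening procedure". Setting and recruitment says when it is applied: "The second phase took place at 72 h, when the result of the CIPA nutrition screening was obtained", and at that point "the patient was verified not to have received nutrition treatment by that time and eventually became part of the sample". The rule is written for both arms.

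Under Interventions, a positive screen leads the attending doctor to consider nutrition treatment. In the control arm the doctor may do so unprompted. Treatment is therefore discretionary in both arms.

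**The concern.** The time to treatment is complete only once treatment has started. A patient who goes home or dies untreated has no value, and none of the named tests has a place for such a patient. Those who do have a value form a subset defined after allocation, and the intervention is designed to alter that subset. Comparing its means sets patients prompted by a screen against patients noticed without one. Adjusting for type, age, sex and medical unit does not restore comparability.

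Length of stay enters as well. Treatment counts only if it precedes discharge, so an arm with shorter stays loses its late starts and looks faster even if prescribing has not changed. Shorter stay is the trial's primary hypothesis.

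The exclusion adds a further problem. Two of the three CIPA components can be known early. For albumin, "This parameter was requested automatically within 48 h post-admission". For BMI or arm circumference, "This data was collected by nurses and nursing assistants, when the patient entered the hospital ward". A patient treated promptly on either result leaves the sample. The Discussion reports that such exclusions were more numerous than foreseen.

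At stake is how the primary result is explained. Readers will look to this endpoint for evidence that screening brought treatment forward.

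**Working it through.** **The plan's own figures.** There is none for this endpoint. The one sample size concerns length of stay and reproduces: (1.960 + 1.282)² × (8² + 13.3²) / 2.6² = 374.4 per arm, and 374.4 × 1.1 = 411.9, or 412. It does not bear on this point.

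**Who is treated (all inputs assumed).** Let control treat 10% of patients at a mean of day 6. Let screening bring the same 10% forward to day 4 and add 15% who would not otherwise be treated, at a mean of day 7.
- Treated-only mean with screening: (0.10×4 + 0.15×7)/0.25 = 5.8 days, against 6.0. The apparent gain is 0.2 days; in comparable patients it is 2 days.
- With the added patients at day 8: (0.40 + 1.20)/0.25 = 6.4 days, an apparent delay of 0.4 days.

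All these times lie beyond 72 h, so the exclusion plays no part here.

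**Stay and exclusion (all inputs assumed).** 30% of patients have a need. Usual care treats them at a rate of 0.1 per day. Stay is 3 days plus an exponential with mean 8 days (discharge rate 0.125 per day after day 3). Patients treated before day 3 are excluded. Screening prompts 70% of those in need. A prompt after 72 h adds a treatment rate of 1 per day from day 3.

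Among retained patients, the mean time to treatment, given that it precedes discharge, is 3 + 1/(treatment rate + discharge rate).
- Control: 3 + 1/(0.1 + 0.125) = 7.44.
- (a) Same prescribing, stay 2.6 days shorter (3 + 5.4): 3 + 1/(0.1 + 1/5.4) = 6.51.
- (b) All prompts after 72 h. Prompted: mean 3 + 1/1.225 = 3.82, probability treated 1.1/1.225 = 0.898. Unprompted: 7.44 and 0.1/0.225 = 0.444. Mixture: (0.7×0.898×3.82 + 0.3×0.444×7.44)/(0.7×0.898 + 0.3×0.444) = 4.45.
- (c) Half the prompts before 72 h: replace 0.7 by 0.35 in (b), giving 4.90.
- (d) All prompts before 72 h: every prompted patient is excluded and the rest behave like control, so 7.44.

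Exclusions are 0.3 × (1 − e^−0.3) = 7.8% in control, (a) and (b); 0.3 × (0.65×0.259 + 0.35) = 15.6% in (c); and 0.3 × (0.3×0.259 + 0.7) = 23.3% in (d).

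| Scenario | Excluded | Treated, of retained | Mean time, retained and treated | Treated by day 5, nobody excluded |
|---|---|---|---|---|
| Control | 7.8% | 10.7% | 7.44 | 11.4% |
| (a) shorter stay only | 7.8% | 8.4% | 6.51 | 11.2% |
| (b) prompts after 72 h | 7.8% | 18.3% | 4.45 | 21.6% |
| (c) half before 72 h | 15.6% | 11.8% | 4.90 | 23.0% |
| (d) all before 72 h | 23.3% | 3.9% | 7.44 | 24.4% |

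The second and last columns come from a simulation of 2,000,000 patients per scenario. It also gave 7.42 for the control mean, sampling noise around the exact 7.44.

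In (d) the mean among all treated patients, with nobody excluded, falls from about 4.8 days to 2.4, yet the retained means are equal. In (a) the means differ by 0.9 days with no change in prescribing. The last column is nearly flat in (a) and rises in (b) to (d), as it should.

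**The case against.** The strongest reply is that the endpoint is a single line in a condensed article. It names no mean and no population, the link to ANCOVA is a general sentence, and the handling of untreated patients may sit in an analysis plan that is not shown. That has force as regards missing detail. It does not answer what the article does state: a method for secondary outcomes that cannot accommodate patients without a value, and an exclusion that removes early values.

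Several further points stand.
- The exclusion applies to both arms, and a common floor does not by itself create a difference.
- A reader might infer that the endpoint cannot show earlier treatment at all. Scenario (b) contradicts this, with a drop of about 3 days.
- A reader might also infer that everyone who screens positive is treated. The Interventions section leaves that to the doctor.
- The floor of about 72 h assumes time counted from admission. For scheduled surgery, screening starts after the operation, so the floor can be later.
- The neighbouring endpoint, the rate of prescribed treatments, does not depend on being treated and would reveal that the treated groups differ in size. The primary endpoint does not depend on this variable.

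**Conclusion.** The point holds in a limited form. A between-arm ANCOVA on time to nutrition treatment conditions on an event that follows allocation and that screening is meant to change. It is not protected by randomisation and can mislead in either direction. It is also blind to earlier treatment inside the 72 h window, although a difference beyond 72 h can still appear.

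The size and direction of the bias cannot be stated from the document. The article gives no treatment rates, no treatment times and no exclusions by arm. The 0.2-day, 0.9-day and 3-day figures illustrate possible behaviour under assumed inputs and are not estimates for this trial. A reader should not conclude that the comparison is certain to hide a gain or that the arms are known to differ in early exclusions.

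This is a secondary endpoint, so the change is one that should be made rather than one on which the primary analysis depends.

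**What to change.** 1. Define the endpoint as time from admission to first nutrition treatment, in all patients in the sample, treated or not.
2. Compare arms by cumulative incidence, with discharge and death as competing events, and report the proportion treated by fixed days.
3. Present the treated-only mean descriptively, not as a between-arm test.
4. Report the number of early-treatment exclusions by arm. If the treatment dates of those consented patients can be retrieved from the medical record, include them in a sensitivity analysis.

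Step 4 matters because steps 1 to 3 repair the conditioning on treatment but not the exclusion. In scenario (d) the share treated among retained patients is 3.9% against 10.7% in control, so even cumulative incidence in the retained sample would point the wrong way. Cumulative incidence also reflects length of stay (8.4% against 10.7% in scenario (a)), so the text should say that it measures the chance of having been treated before leaving hospital.

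**Cost.** For the retained sample the cost is revised analysis wording and slightly more work, because treatment start, discharge and in-hospital death are already needed for other endpoints. Adding early-treated patients may cost more. They consented at admission and clinical data come from the medical record, but they never entered the sample, and the article does not say that their data were kept.

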##### Quality of life

Health-related quality of life (HRQoL) was measured using the EQ-5D-5 L questionnaire. This generic, self-reported description assesses five domains: mobility, self-care, usual activity, pain or discomfort, and anxiety or depression. Each dimension is scored on a scale of 1 to 5, depending on whether the respondent has no problems, slight, moderate, severe, or extreme problems with each dimension. This descriptive system defines 3125 health states. Each health state can then be converted into a single summary index by applying a formula that associates weights to each state, based on evaluations from general population samples, developed by the EuroQoL group. Upon application of these weights, an EQ-5D index score of one represents full health, a score of zero is equivalent to death, and negative scores represent health states worse than death [17].

##### Biochemical determinations

Plasma albumin was determined by colorimetry, using a Roche/Hitachi Cobas C 702 Autoanalyzer (Roche Diagnostics). This parameter was requested automatically within 48 h post-admission. Results are expressed in g/dL.

##### Anthropometric determinations

BMI: Weight (kg) and height (cm) were obtained with the patient barefoot, dressed in hospital pajamas, using calibrated Seca 220 scales that include a height rod. In the case of patients confined to bed, where weight and height could not be determined, MUAC (cm) was obtained on the patient’s non-dominant arm, at the midpoint between the acromion and olecranon, surrounding the arm with a measuring tape (Seca 201) without pressing the limb. This data was collected by nurses and nursing assistants, when the patient entered the hospital ward, and was then transferred to the electronic medical record (EMR).

##### Health care utilization

Health care utilization includes staff time and material required to implement the malnutrition screening tool CIPA, duration of tube feeding or any other nutritional treatment, visits from other specialists during hospitalization, in-hospital complications, hospital length of stay, and readmissions and other health care contacts within 3 months after discharge.

In addition, the following patient information was collected upon admission: initials, the assigned ward, clinical record, nationality, age, sex, type of admission (emergency or scheduled), date of and diagnosis on admission. Subsequently, the diagnosis-related group (DRG) as well as the severity-based DRG were established.

### Measurement procedures

Data collection is being managed using an electronic case report form (CRF), designed for this study and complemented with EMR information and patient questionnaires conducted by phone 3 months past discharge.

The project data manager compiles all clinical data from the EMR, except for the EQ-5D-5 L questionnaires, which are being collected at hospital admission, discharge, and 3 months post-discharge, and the DRG and severity-based DRG, which are presented by the Management Unit following hospital discharge. The main data and laboratory parameters of included patients are directly recorded in the CRF. The CI and the CHADx and Clavien-Dindo classifications are documented by the medical staff subsequent to the patient’s discharge.

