### Random assignment

Both scheduled and emergency admission patients were allocated by the department of hospital admission to one of the participating wards, following the randomization plan, which was generated by simple random sampling and delivered by the data manager of the project. This randomization facilitated trial execution and prevented protocol errors, as the group to which each patient belonged was defined by its location.

Both the Internal Medicine and the General and Digestive Surgery ward are divided into two hospitalization wings. At the time of the study, due to the progressive introduction of the nutrition screening in the HUNSC, one of the two wings of either ward conducted the CIPA screening at hospital admission (intervention wards), while the other did not (control wards, where standard practice was performed).

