### Blinding

Due to the nature of the intervention, neither enrolled patients nor the clinical research team could have been blinded to the group they belonged to, although patients were not informed until they signed the consent of their group. The doctors responsible for treatment did not know whether or not patients were enrolled in the study for not to create an intervention bias on the patient. Data analysis is going to be blinded to the intervention assignment.

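### Complications are classified after discharge by medical staff with no masking described, in a trial where the wing reveals the arm, so the CHADx and Clavien-Dindo comparisons are open to assessor bias

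*Protocol article*

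**What the plan says.** - **Who classifies, and when.** Under Measurement procedures: "The CI and the CHADx and Clavien-Dindo classifications are documented by the medical staff subsequent to the" patient's discharge. No masking, extract or adjudication step is mentioned.
- **Who is blinded.** Under Blinding, "neither enrolled patients nor the clinical research team could have been blinded to the group they belonged to". The same section adds: "The doctors responsible for treatment did not know whether or not patients were enrolled in the study". The one blinded step is the last: "Data analysis is going to be blinded to the intervention assignment".
- **How visible the arm is.** Under Random assignment, "the group to which each patient belonged was defined by its location". One wing of each ward ran CIPA and the other did not. The assigned ward is also among the data collected for each patient (Health care utilization).
- **What the classifications feed.** The Complications section makes CHADx incidence and the highest Clavien-Dindo grade per patient secondary endpoints. Health care utilization lists in-hospital complications as a component, and the Cost-effectiveness analysis section gives every component a unit cost.
- **What is measured in each arm.** Under Interventions, CIPA patients have food intake, albumin and BMI or arm circumference assessed as routine. For controls, the responsible doctor may ask for nutrition parameters.

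**The concern.** Grading the severity of a surgical complication involves judgement, and so may deciding which in-stay events count as complications. If the person judging knows the arm, expectation can shift the result. Clavien-Dindo keeps only the worst grade per patient, so one decision can change that patient's outcome. Blinding the analyst comes too late, because the data would already carry the assessor's knowledge.

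A second, conditional route is unequal ascertainment. If nutritional status is looked for systematically in one arm only, and if CHADx counts the resulting diagnoses as acquired in hospital, the CIPA arm could show more complications without any true difference. The two routes may pull in opposite directions, and nothing ensures that they cancel.

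At stake are the complication comparisons and, through the unit costs, the complication part of the incremental cost.

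**Working it through.** The article gives no complication rate, so the main check sets its statements side by side.

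**1. Could the classifiers be unaware of the arm?** The article does not say which medical staff classify. There are three possibilities:

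- *Research team:* the Blinding section states that it is not blinded.
- *Treating doctors:* they are said not to know who is enrolled, but they know the wing they work in, and the wing is the arm. Completing trial classifications would also tell them who was enrolled. This happens after discharge, so it need not affect care, but it does not mask the grading.
- *Other staff:* they could be masked, but no such step is described and the assigned ward is part of the collected data.

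Masking is stated under none of the three. That the classifiers know the arm is an inference from Random assignment and Blinding, not a statement in Measurement procedures.

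**2. Does unequal measurement reach CHADx?**

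- For: measurement is systematic in the CIPA arm and discretionary in controls (Interventions). The Discussion calls general albumin testing the only extra cost of CIPA, which suggests that it is not routine otherwise.
- Against: the sections on biochemical and anthropometric determinations describe automatic albumin requests within 48 h and measurement on ward entry without naming an arm.
- Undetermined: CHADx is described as a classification of hospital-acquired diagnoses built on ICD-10 codes. The article gives no code list and no rule for findings present on admission. A low BMI on ward entry, or low albumin within 48 h, might be treated as pre-existing.

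This route is therefore possible but not established.

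**3. What is not touched.** The primary endpoint is length of stay. Its sample size reproduces without any complication input:

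n = (8² + 13.3²) × (1.960 + 1.282)² / 2.6² = 374.4 per arm; 374.4 × 1.10 = 411.9, i.e. 412.

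**4. Illustration with assumed rates.** Let the true complication rate be p in both arms, and let e be extra recording in the CIPA arm. The chance of a false significant difference at two-sided 5% with n = 412 per arm is about Φ((e − 1.96·SE₀)/SE₁). Here SE₀ = √(2p̄(1−p̄)/n), p̄ = p + e/2, and SE₁ = √([p(1−p) + (p+e)(1−p−e)]/n).

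For p = 0.10 and e = 0.05: SE₀ = 0.02304, SE₁ = 0.02298, and Φ((0.05 − 0.04516)/0.02298) = Φ(0.21) = 0.58.

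| Assumed p | e = 2 points | e = 5 points |
|---|---|---|
| 10% | 0.15 | 0.58 |
| 20% | 0.11 | 0.40 |
| 30% | 0.09 | 0.33 |
| 40% | 0.08 | 0.31 |

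Read in reverse (true rate p + e in both arms, e points lost in the CIPA arm), the same figures describe under-recording. The table shows only that shifts of a few points would matter. It is not an estimate of the bias.

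**The case against.** The strongest reply is that a condensed article may leave masking of outcome classification to the full protocol, that treating doctors did not know who was enrolled, and that only secondary outcomes are involved. The last part stands and limits the point. The second does not help, since ignorance of enrolment is not ignorance of the arm. The first stands in part: if the full protocol masks the classifiers, the remedy is one sentence saying so. But the article does fix who classifies, when, and which step is blinded, and on that text the outcome is not protected.

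A reader might infer more than the article supports:

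- *That CIPA findings are in fact counted as complications more often in the intervention arm.* This needs the CHADx code list and a present-on-admission rule, and neither is given.
- *That the bias can be sized.* The mortality percentages in the Background (7.6% and 12.7% against 1.4% and 3.5%) fit 79 positive and 142 negative patients. If these are the 221 patients mentioned in the Discussion, 79/221 = 35.7% were CIPA-positive. Multiplying that share by a coding rate requires a rate that the article lacks. The 221 were also non-surgical, whereas this trial includes surgical patients and excludes those given nutrition support before screening ends.
- *That the severity-based DRG would be distorted with consequences for the trial.* It is collected, but it is not named as an endpoint or covariate, and costs are built from unit costs of utilization components.
- *That coded discharge diagnoses would lose events equally in both arms.* The codes would still come from records kept on open wards, so this cannot be assumed.

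**Conclusion.** The concern holds as a risk of assessor bias in the CHADx and Clavien-Dindo outcomes and in the complication cost component. It rests on the article's statements that medical staff classify after discharge, that location defines the arm and that only the analysis is blinded. It also rests on the inference that no unreported masking exists. Differential coding through unequal nutrition measurement is a further possibility, conditional on CHADx counting nutrition-related diagnoses. Neither the direction nor the size of the net bias can be derived from the article. The primary endpoint and the sample size are unaffected. This is a worthwhile, inexpensive improvement to secondary outcomes and does not threaten the trial's main comparison.

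**What to change.** The article reports that data are still being collected, so the following could be fixed before the analysis:

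1. Have the existing staff grade Clavien-Dindo from extracts with the wing, the CIPA result and dietitian entries removed.
2. Assign CHADx by applying its ICD-10 mapping by rule to coded discharge diagnoses, where these are available, instead of by arm-aware judgement. The Management Unit supplies the DRGs after discharge and is an obvious place to ask, although the article does not say that it holds the underlying codes.
3. Check whether any nutrition-related codes fall within CHADx. If so, report the complication comparison with and without them.
4. State in the Blinding section who classifies complications and what they can see.

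The cost is staff time to prepare masked extracts and a mapping routine. No new patients or assessors are needed. Discharge codes may miss minor events and will still reflect open-ward recording, so these steps reduce the bias and do not remove it.
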